# Transcranial alternating current stimulation improves quality of life in Parkinson’s disease: study protocol for a randomized, double-blind, controlled trial

**DOI:** 10.1186/s13063-024-08045-5

**Published:** 2024-03-20

**Keywords:** Transcranial alternating current stimulation, Parkinson’ s disease, Multidisciplinary intensive rehabilitation treatment, Randomized controlled trial

## Abstract

**Background:**

The neural cells in the brains of patients with Parkinson’s disease (PWP) display aberrant synchronized oscillatory activity within the beta frequency range. Additionally, enhanced gamma oscillations may serve as a compensatory mechanism for motor inhibition mediated by beta activity and also reinstate plasticity in the primary motor cortex affected by Parkinson’s disease. Transcranial alternating current stimulation (tACS) can synchronize endogenous oscillations with exogenous rhythms, thereby modulating cortical activity. The objective of this study is to investigate whether the addition of tACS to multidisciplinary intensive rehabilitation treatment (MIRT) can improve symptoms of PWP so as to enhance the quality of life in individuals with Parkinson’s disease based on the central-peripheral-central theory.

**Methods:**

The present study was a randomized, double-blind trial that enrolled 60 individuals with Parkinson’s disease aged between 45 and 70 years, who had Hoehn-Yahr scale scores ranging from 1 to 3. Participants were randomly assigned in a 1:1 ratio to either the tACS + MIRT group or the sham-tACS + MIRT group. The trial consisted of a two-week double-blind treatment period followed by a 24-week follow-up period, resulting in a total duration of twenty-six weeks. The primary outcome measured the change in PDQ-39 scores from baseline (T0) to 4 weeks (T2), 12 weeks (T3), and 24 weeks (T4) after completion of the intervention. The secondary outcome assessed changes in MDS-UPDRS III scores at T0, the end of intervention (T1), T2, T3, and T4. Additional clinical assessments and mechanistic studies were conducted as tertiary outcomes.

**Discussion:**

The objective of this study is to demonstrate that tACS can enhance overall functionality and improve quality of life in PWP, based on the framework of MIRT. Additionally, it seeks to establish a potential correlation between these therapeutic effects and neuroplasticity alterations in relevant brain regions. The efficacy of tACS will be assessed during the follow-up period in order to optimize neuroplasticity and enhance its potential impact on rehabilitation efficiency for PWP.

**Trial registration:**

Chinese Clinical Trial Registry ChiCTR2300071969. Registered on 30 May 2023.

**Supplementary Information:**

The online version contains supplementary material available at 10.1186/s13063-024-08045-5.

## Administrative information

Note: the numbers in curly brackets in this protocol refer to the SPIRIT checklist item numbers. The order of the items has been modified to group similar items (see https://www.equator-network.org/reporting-guidelines/spirit-2013-statement-defining-standard-protocol-itemsfor-clinical-trials/).

## Introduction

### Background and rationale {6a}

Parkinson’s disease (PD) is a common neurodegenerative disease whose clinical manifestations include motor and non-motor symptoms [1]. Motor symptoms comprise resting tremor, bradykinesia, gait disturbance, and myotonia. Non-motor symptoms encompass cognitive dysfunction, sensory abnormalities, depression, anxiety, and autonomic dysfunction [2–4]. These symptoms have a significant impact on the quality of life of patients and result in substantial medical expenses [5, 6]. Neuronal oscillations in the brain play a key role in the pathophysiology of PD. Specific frequency patterns can control communication and network resonance between brain regions, and rapid pathological neuronal synchronization in PD may be a causative factor for motor and non-motor disorders [7, 8]. Abnormal synchronized beta oscillatory activity has been observed at multiple levels within the basal ganglia network in both people with Parkinson’s disease and animal models [9, 10]. The beta activity is associated with symptoms of Parkinson’s disease, such as rigidity and bradykinesia, and can be modulated by medication and deep brain stimulation (DBS). Suppression of beta power is also correlated with improvement in dyskinesia. In humans undergoing invasive recordings, both levodopa and therapeutic DBS have demonstrated the ability to decrease oscillatory synchronization within the beta range (13–30 Hz), while simultaneously promoting oscillatory synchronization within the gamma range (60–90 Hz) across multiple structures within the motor network [11–14]. The gamma band activity is generally considered to have a prokinetic effect, serving as a compensatory mechanism for the akinetic role played by beta activity [15, 16]. Increased gamma power has been observed at the initiation of exercise [17], during exercise [18], and during motor imagery [19]. Studies have demonstrated that cortical gamma oscillations play a beneficial role in modulating the long-term potentiation-like plasticity of M1 in Parkinson’s disease and improve motor symptoms in PWP [20, 21].

Transcranial alternating current stimulation (tACS), a non-invasive stimulation technique, is capable of modulating cortical activity by manipulating and entraining intrinsic oscillations through the injection of sinusoidal alternating current from the scalp, with the endogenous oscillations during entrainment synchronized with the extrinsic rhythmic stimulation [22, 23]. The extracellular application of alternating current (AC) electric field in tACS modulates neuronal transmembrane potentials at the cellular level, inducing sinusoidal changes. Even small polarizations of the cell membrane can significantly impact the firing rate of active neurons, while AC stimulation effects can be further amplified by neuronal networks [24, 25]. In recent years, mounting evidence suggests that tACS can modulate cortical rhythms by entraining endogenous oscillations and promote neuroplasticity in multiple brain regions, thereby enhancing motor function and alleviating non-motor symptoms in individuals with PWP [21, 26–29]. For security reasons, previous studies on the application of tACS in PWP have primarily focused on utilizing weak currents below 2 mA. Although these studies have demonstrated some efficacy in improving bradykinesia, tremor, and cognition among PWP [27, 30, 31], they have generally employed low energy levels and limited cortical region stimulation through single stimuli. Furthermore, the conclusions regarding long-term effects have been inconsistent [32]. Several recent studies have shown that high-intensity transcranial alternating current stimulation (Hi-tACS) with parameters of 77.5 Hz (gamma band) and 15 mA may be more potent inducers of certain deep brain regions and have been shown to be safe. The delivery of a current with a frequency of 77.5 Hz through electrodes placed on the forehead and mastoid areas has been reported to modulate beta-endorphin and neurotransmitter levels in the cerebrospinal fluid, brainstem, hypothalamus, and cortex [33, 34]. It has demonstrated efficacy in ameliorating chronic primary insomnia, refractory epilepsy, as well as anxiety and depression, while maintaining a proven safety profile [35–37]. However, the effectiveness and neurobiological mechanisms of Hi-tACS in improving motor and non-motor functions in PWP have not been investigated. It is crucial to explore the role of Hi-tACS as a large alternating current in Parkinson’s disease in terms of motor and non-motor symptoms, and quality of life.

The “central-peripheral-central” closed-loop rehabilitation theory is a comprehensive framework for rehabilitation, wherein central neuroplasticity activation facilitates the formation of a feedback loop to enhance or restore damaged neural pathways [38]. By stimulating the central nervous system, neuroplasticity can be promoted to improve or reestablish impaired neural connections. Additionally, peripheral nervous system activation enhances central nervous system control by transmitting sensory information, activating muscles, and improving blood circulation. This integrated approach aims to achieve overall rehabilitation effects. Multidisciplinary intensive rehabilitation therapy (MIRT) is a comprehensive program for PWP that encompasses various disciplines such as aerobic exercise and motor cognitive therapy. It emphasizes combining balance exercises with cognitively demanding motor tasks (dual-tasking) [39–43].

Therefore, our hypothesis is that the combination of MIRT with tACS could potentially augment the management of motor and non-motor symptoms in PWP and optimize the efficiency and efficacy of rehabilitation therapy, thereby ultimately improving the overall quality of life for individuals affected by PD. The effectiveness of tACS in treating PWP has been validated through a randomized controlled trial (RCT) involving both true and sham stimulation groups. Additionally, we have investigated the neural mechanism underlying tACS-induced amelioration of Parkinson’s disease symptoms using behavioral indices, neuroelectrophysiology, functional magnetic resonance imaging (fMRI), and biomarkers. This study aims to establish a theoretical foundation for developing an innovative rehabilitation treatment plan for Parkinson’s disease while implementing tACS stimulation protocols.

### Objectives {7}

#### Primary objective

To investigate the impact of tACS on improving the quality of life in PWP.

#### Secondary objective

To investigate the effect of tACS on motor and non-motor symptoms in PWP.To establish a correlation between the amelioration of behavioral outcomes and alterations in functional connectivity of neural networks, as well as biomarkers indicative of neuroplasticity, while investigating the underlying mechanisms of neuroplasticity associated with rehabilitation interventions.

### Trial design {8}

The study will be a double-blind, randomized, placebo-controlled trial. The present protocol follows the Standard Protocol Items Recommendations for Interventional Trials (SPIRIT) guidelines and fulfills the SPIRIT checklist [44]. Our hypothesis is that tACS combined with MIRT is superior in terms of efficiency and effectiveness compared to MIRT alone for treating PD. Each patient’s participation in the study will last for 26 weeks, including baseline evaluation (T0), a 10-day intervention period, and assessments at the end of intervention (T1), as well as 4 weeks (T2), 12 weeks (T3), and 24 weeks (T4) post-intervention. Please refer to Fig. 1 for details regarding patient visits and follow-up schedule. Additionally, Fig. 2 provides an overview of all interventions and outcome measures in accordance with SPIRIT 2013 guidelines [45] (Additional file 1).

**Fig. 1 Fig1:**
[figure not shown]
Flow chart of the experimental design

**Fig. 2 Fig2:**
[figure not shown]
Schedule of enrolment, interventions, and assessments in accordance with the SPIRIT 2013 guidelines. LEDD, levodopa equivalent daily dose; tACS, transcranial alternating current stimulation; MIRT, multidisciplinary intensive rehabilitation treatment; PDQ-39, 39-item Parkinson’s Disease Questionnaire; EEG, electroencephalogram; fMRI, functional magnetic resonance imaging

## Methods: participants, interventions, and outcomes

### Study setting {9}

This study will be conducted at a single site: Beijing Rehabilitation Hospital, Capital Medical University. The Department of Scientific Research Management of Beijing Rehabilitation Hospital was responsible for overseeing the trial.

### Eligibility criteria {10}

The recruitment of PWP will be conducted through the outpatient clinic of Beijing Rehabilitation Hospital, Capital Medical University, as well as via the hospital website. Participants will be randomly assigned to either the tACS + MIRT group or sham-tACS + MIRT group in a 1:1 ratio, with 30 participants in each group. The trial group’s recruitment and intervention procedures will take place at Beijing Rehabilitation Hospital, Capital Medical University. Follow-up evaluations at each time point will be carried out either through an online follow-up system or within the outpatient clinic.

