#### Secondary outcome

The secondary outcome will encompass changes in motor symptom scales such as the third part of the Movement Disorders-Unified Parkinson’s Disease Rating Scale (MDS-UPDRS III) [49], Mini-balance evaluation systems test (Mini-BES Test) [50], and 6-min walking test (6MWT) [51] from T0 to T1, T2, T3, and T4. Additionally, alterations in non-motor symptom scales such as non-motor symptoms scale (NMSS) [52], Montreal cognitive assessment (MoCA) [53], and Hamilton depression scale (HAMD) [54] from T0 to T2, T3, and T4 will be evaluated.

MDS-UPDRS III comprises of 18 items designed to evaluate motor function in individuals with Parkinson’s disease (PWP). The Chinese version of the MDS-UPDRS III demonstrates excellent reliability and validity, exhibiting a strong correlation with the conventional UPDRS [55].Mini-BES test is utilized for assessing gait and postural stability. This scale has demonstrated excellent inter-rater reliability (intraclass correlation coefficient (ICC) > 0.95) as well as high test-retest reliability (ICC > 0.95) [56].6MWT measures the distance that a patient can quickly walk on a flat, hard surface within 6 min. We used the validated Chinese version which has shown a very high inter-rater correlation coefficient (ICC = 0:99) [57].NMSS allows quantitative evaluation of NMS of PD. The Chinese version of the NMSS can be considered a comprehensive, useful measure for NMS evaluation in Chinese PWP (Cronbach’s coefficient = 0.89, ICC = 0.99) [58].MoCA is a screening tool for mild cognitive impairment. The reliability of the Chinese version of MoCA has been proven in the clinic [59].HAMD will be utilized for the evaluation of a patient’s anxiety and depression levels. Its Chinese version has been empirically validated as a reliable and valid assessment tool [60].

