## Data collection and management

### Plans for assessment and collection of outcomes {18a}

The following data will be collected at baseline: gender, age, occupation, educational level, current medication status, and detailed physical and neurological examinations. Inclusion and exclusion criteria will be evaluated. PDQ-39 assessments will be conducted at T0, T2, T3, and T4. MDS-UPDRS III [49, 55], Mini-BES test [50, 56], 6MWT [51, 57], NMSS [52, 58], MoCA [53, 59], and HAMD, as well as other motor symptom scales and non-motor symptom scales, will be assessed at T0, T1, T2, T3, and T4 respectively. MRI and EEG scans will be evaluated at T0 and T1. Levodopa equivalent daily dose (LEDD) data will be collected at T0, T1, T2, T3, and T4. All these assessments will be conducted in a double-blind manner by raters who were unaware of the treatment administered to the patients. At T0 and T1, various safety indicators including blood routine, urine routine, stool routine, liver and kidney function tests, electrocardiogram readings, and other relevant parameters will be evaluated. Any adverse events occurring during the study will be documented. Participants will be asked for their consent regarding the use of their data if they choose to withdraw from the trial. Additionally, participants must obtain permission from the research team to share their pertinent information with university personnel involved in the study or relevant regulatory authorities. Prior to commencing the study, investigators will undergo standardized training on data collection strategies as well as guidelines for utilizing different scales to assess outcomes. Throughout the trial period, professionally trained researchers will collect data to ensure impartiality. In case subjects experience an “on–off” phenomenon during treatment response fluctuations; separate data collection sessions will take place during both “on” and “off” periods for subsequent comparison.

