### Methods in analysis to handle protocol non-adherence and any statistical methods to handle missing data {20c}

The intention-to-treat (ITT) analysis will be the primary analysis of this study, with per-protocol (PP) analysis as a secondary analysis in case patients were unable to receive the intervention due to issues related to the intervention itself, such as adverse effects, difficult administration, or adherence problems. Missing data will be handled using the last observation carried forward (LOCF) method. Sensitivity analyses will be conducted if there are imbalanced losses to follow up or excessive attrition.

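### Follow-up visits may be online or in clinic with no rule by assessment, so motor tests not done at T2–T4 could be filled by LOCF with earlier clinic scores

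*Protocol article*

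**What the plan says.** **Visit mode.** Under Eligibility criteria {10}: "Follow-up evaluations at each time point will be carried out either through an online follow-up system or within the outpatient clinic". Neither that section nor any other in the article says which assessments need attendance. The same section places treatment at the hospital ("The trial group’s recruitment and intervention procedures will take place at Beijing Rehabilitation Hospital, Capital Medical University"), so the end-of-treatment assessment T1 can be taken as on site.

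**Timing.** Trial design {8} sets "assessments at the end of intervention (T1), as well as 4 weeks (T2), 12 weeks (T3), and 24 weeks (T4) post-intervention".

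**Motor outcomes.** The Secondary outcome section lists MDS-UPDRS III, the Mini-BES Test and the "6-min walking test (6MWT) [51] from T0 to T1, T2, T3, and T4". Plans for assessment and collection of outcomes {18a} repeats that the motor scales "will be assessed at T0, T1, T2, T3, and T4 respectively". The 6MWT is described physically: "6MWT measures the distance that a patient can quickly walk on a flat, hard surface within 6 min". The Mini-BES Test is described as a test of walking and postural control. No remote version of any of the three is described.

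**Missing values.** Section {20c}: "Missing data will be handled using the last observation carried forward (LOCF) method". No outcome is exempt. Sensitivity analyses are promised only if losses differ between arms or attrition is excessive.

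**The concern.** Each of these statements is unremarkable alone. Together they leave a gap. A visit may be held in a mode in which at least two scheduled tests cannot be done as the article describes them, nothing says what then happens to those tests, and the general missing-data rule fills the empty cell with an earlier score. For a patient with no motor test after T1, that score was taken at the end of a 10-day treatment course, when a stimulation effect would probably be near its largest.

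The Discussion says the trial will establish long-term effects on quality of life and overall functioning, and the Abstract names change in MDS-UPDRS III through T4 as the secondary outcome. If part of the T4 motor comparison is a copy of the T1 comparison, it cannot separate persistence from fading. The planned sensitivity analyses need not expose this, because a patient who is seen online has not been lost to follow-up.

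**Working it through.** **1. The plan's own figure.** Sample size {14} inflates 27 per group for 10% attrition: 27 / (1 − 0.10) = 30, as stated. The 27 itself cannot be rebuilt, since no effect or SD is given. At two-sided α = 0.05 (sidedness is not stated) and power 0.90 it implies a standardised difference of (1.960 + 1.282) × √(2/27) = 0.88. That figure belongs to PDQ-39. It is used below only as a guide to a plausible effect size, not as a motor effect taken from the article.

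**2. Tracing a motor value at T4.**

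| Situation | Value analysed at T4 |
|---|---|
| Motor test done in clinic at T4 | Observed T4 score |
| No test at T4, test done at T3 | T3 score carried forward |
| No test at T4 or T3, test done at T2 | T2 score carried forward |
| No test at T2, T3 or T4 | T1 score carried forward |
| Test done remotely at T4 | Observed, but in a different measurement mode |

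**3. Effect on the contrast.** Let D1 and D4 be the true between-arm differences at T1 and T4, and p the share per arm in the fourth row, with all others observed at T4. Assume that p is the same in both arms and unrelated to the size of the effect. Then:

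expected LOCF contrast at T4 = (1 − p)·D4 + p·D1

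The article gives none of p, D1 or D4. As multiples of D1:

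| p | D4 = 0 | D4 = 0.5·D1 |
|---|---|---|
| 0 | 0 | 0.50 |
| 0.10 | 0.10 | 0.55 |
| 0.25 | 0.25 | 0.625 |
| 0.50 | 0.50 | 0.75 |
| 1.00 | 1.00 | 1.00 |

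**4. An illustration in SD units.** Take D1 = 0.9 SD (close to the 0.88 in step 1) and D4 = 0:

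- p = 0.10: 0.10 × 0.9 = 0.09 SD
- p = 0.25: 0.25 × 0.9 = 0.225, about 0.23 SD
- p = 0.50: 0.50 × 0.9 = 0.45 SD

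In a simulation of 20,000 trials with 30 per arm under these inputs, a significant T4 result favouring tACS occurred in 4.9%, 13% and 37% of trials, against a nominal 2.5% in that direction.

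**5. The primary outcome.** PDQ-39 is a questionnaire collected at T0, T2, T3 and T4. It can be completed online and has no T1 value to carry forward, so this mechanism does not reach it.

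**The case against.** The strongest reply is that the plan can be carried out without any of this happening. The assessment section requires the motor tests at T2, T3 and T4, the clinic route is available, and staff may use the online system only for questionnaires. An either/or statement about visits does not exclude that. A condensed article may also leave visit mode to the full protocol, and the schedule figure, which is not shown, might specify it.

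Much of this stands. A reader might infer that every follow-up visit will be online and that T1 motor scores will therefore be reported as 24-week results. The documents do not support that. They nowhere say that motor tests are skipped at an online visit. T1 reaches T4 only if a patient has no motor test at T2, T3 and T4 alike, since one clinic test at T2 or T3 becomes the carried value and one at T4 removes imputation there. A reader might also infer that the plan rules out keeping online contact for questionnaires; it is silent on the matter. Remote rating of at least part of MDS-UPDRS III is not excluded, so the point is firmest for the 6MWT and the Mini-BES Test. If tests were done remotely, the problem would be mixed measurement modes, not LOCF. A difference in visit mode between arms would be conjecture in a trial that blinds participants and assessors.

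The reply does not remove the gap. The visit-mode sentence is stated text that covers every follow-up time point without restriction, and LOCF is stated without exception. A team following both as written may produce carried-forward motor scores at T4.

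**Conclusion.** The point holds in limited form. The article leaves visit mode unreconciled with performance tests due at T2–T4, and its LOCF rule could then report an earlier clinic score as a 24-week result. The direction is predictable: if the effect fades after treatment, the T4 motor contrast is pulled towards the T1 contrast by the fraction p. The size is unknown because p is not stated. It is zero if all motor tests are done in clinic, and 0.09 to 0.45 SD for p from 0.10 to 0.50 under the assumed D1 = 0.9 SD and D4 = 0. These values, and the simulated error rates, describe the assumed inputs and are not a forecast for this trial.

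The damage is confined to secondary motor outcomes. The change is worth making because those outcomes carry the motor part of the long-term claim and the correction is cheap, but the primary comparison is not threatened by this mechanism.

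**What to change.** Reconcile Eligibility criteria {10}, the Secondary outcome section, {18a} and {20c}:

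- State that the 6MWT and Mini-BES Test at T2, T3 and T4 are done at the outpatient clinic, and likewise MDS-UPDRS III unless a remote version is specified. Limit online contact to questionnaires such as PDQ-39.
- Replace LOCF for these three outcomes with a repeated-measures model fitted to the observed scores, so that a test not done stays missing and is not replaced by a T1 score.

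The cost is a few sentences of protocol text, an amended analysis rule, and clinic attendance at T2–T4 for some patients who would otherwise have been seen online. That extra travel could itself lose some visits. The repeated-measures model handles such losses under a missing-at-random assumption, which should be stated. The clinic route is already provided for, so no new facility is needed.
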